### Data collection

At baseline and 3, 6, 9 and 12 months, respectively, from the participant’s inclusion in the study, an email containing a link to an online questionnaire will be sent to the participants. All collected data will be self-reports, including a 30 s chair stand self-test (30CST). In the absence of completed questionnaires, a reminding email will be sent out after 1 week. If further absence, another email will be sent after an additional week. This reminder will also include a question if they want to withdraw from the study. Data registered in the exercise diary of the application are collected continuously. In the same monthly email as the educational videos, all participants will receive a request to report any falls during the past month by answering a short web-based questionnaire. In the absence of a completed questionnaire, one reminder will be sent after 1 week. All data retrieved from questionnaires, as well as application data, will be coded and reported on a group level.

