### Outcomes

#### Primary outcome

The primary and secondary outcomes, and time points of distribution are presented in table 2. The primary outcome measure will be the rate of falls (fall per person/year) during the 12 months of the intervention. To register falls, a link to a self-report online questionnaire will be sent monthly by email. To be able to report correctly the coming month, participants are asked to make notes of falls in a calendar, preferably the day the fall has occurred. They will be provided with a printable calendar in the email sent out after allocation, but they can also use their own. If a fall is reported, additional questions will be asked about the cause of the fall, potential injuries sustained, need for medical attention and hospitalisation. The number of persons falling during 12 months will be analysed based on the same data as a secondary outcome.

**Table 2 T2:** List of primary and secondary outcome measures

Outcome measures	BA	C	M	3 months	6 months	9 months	12 months
Fall rate† (fall per person/year)			X				
Number of fallers‡ (n)			X				
Number of falls during exercise with Safe Step§ (n)			X				
Fall-related injuries§ (yes/no, need of medical attention, type of injury)			X				
Hospitalisation due to falls§ (yes/no and number of days)			X				
Reach§ (self-reported sociodemographic parameters such as age, sex, years of education, use of smartphone and tablet, number of cohabitants and self-reported health and diagnosis)	X						
Self-administered 30 s chair stand test¶	X			X	X	X	X
The Borg Scale of Perceived Exertion during 30 s chair stand test** (numeric scale, score 6–20)	X			X	X	X	X
Self-rated balance**, ‘How do you perceive your balance?’ (5-level ordinal scale)	X			X	X	X	X
Self-rated leg strength**, ‘How do you perceive your leg muscle strength?’ (5-level ordinal scale)	X			X	X	X	X
Fear of falling¶ (Falls Efficacy Scale-International)	X			X	X	X	X
Health-related quality of life¶ (EQ-5D-5L)	X			X	X	X	X
Experienced positive effects of the exercise intervention§ (nominal scale, optional text field)	X*			X*	X*	X*	X*
Experienced negative effects of the exercise intervention§ (nominal scale, optional text field)	X*			X*	X*	X*	X*
Exercise adherence throughout the intervention reported through an integrated exercise diary in the Safe Step application§,¶		X*					
Exercise adherence, self-reported min/week§				X*	X*	X*	X*
Use and perceived usefulness of educational videos** (4-level ordinal scale)				X	X	X	X

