Self-rated improvements in balance††, ‘If you compare with when you started this study a year ago, how would you assess balance today?’ (5-level ordinal scale)							X
Self-rated improvements in leg-strength††, ‘If you compare with when you started this study a year ago, how would you assess the muscle strength in your legs today?’ (5-level ordinal scale)							X
Rate of attrition‡ (n)							X
New exercise routines§ (yes/no, text field to describe the exercise, time since initiation (predefined alternatives), min/week (predefined alternatives))							X
Physical activity¶ (min/week, predefined alternatives)	X						X
Self-reported costs related to the interventions§ (amount and what)							X
Cost effectiveness of the interventions with respect to falls¶							X

*Only administered to the exercise intervention group,

†Negative binomial regression.

‡Logistic regression.

§Descriptive analysis.

¶Linear mixed model.

**Cumulative link mixed model.

††Ordinal logistic regression.

BA, baseline assessment; C, continuously; EQ-5D-5L, European Quality of Life, 5 dimensions; M, monthly administered.

Falls will be defined as an event in which the person comes to rest inadvertently on the ground or floor, regardless of what caused the fall or if an injury was sustained. Our definition is slightly modified and clarified in comparison with a previous consensus statement.^30^ The ProFaNE definition included falls where the person come to rest on an ‘other lower level’, for example, tripping and taking a hold of a dresser.^30^ We exclude ‘lower level’ as our experience from previous studies is that participants seldom perceived such an event as a fall. In accordance with a systematic review,^38^ we clarify that a fall should be reported regardless of cause and we also clarify that unintentionally coming to rest on the floor or ground is a fall regardless of injury. Our definition is printed in the online questionnaire.

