Additional questions will be asked to the exercise intervention group regarding adherence, experienced positive effects besides strength and balance, and adverse events. Adherence to exercise will be evaluated by self-report questions at follow-up assessments through predefined alternatives, and will be summarised as exercised min/week. Additionally, adherence to exercise including the proportion meeting at least the predefined minutes of 3×30 min/week, will be collected through an exercise diary integrated within the Safe Step-application.

At self-report assessments at 3, 6, 9 and 12 months after study start, a single-item question with predefined answers will be used to assess experienced positive effects of the exercise intervention besides effects on balance and strength.

Adverse events in form of falls occurring while exercising with the Safe Step application will be monitored monthly. If a participant registers a fall in the monthly questionnaire, there will be a follow-up question of whether the fall occurred while exercising with the Safe Step programme. If so, a member of the research team will contact the participant to ask him or her about the nature of the fall, and if necessary, suggest measures to prevent further falls during exercise. Additional adverse events of taking part in the intervention (eg, muscle strain) will be collected at assessments at 3, 6, 9 and 12 months after study start, and measured through a single-item question: ‘Have you experienced any negative effects of the exercise intervention?’ The participants will be presented with predefined alternatives and an optional text field.

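### Adverse events that do not arise from a fall are counted in the exercise arm only, by a self-attribution question, so the plan gives no randomised comparison for them

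*Protocol article*

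**What the plan says.** The Secondary outcomes section of the protocol article introduces the harms questions as specific to one arm: "Additional questions will be asked to the exercise intervention group regarding adherence, experienced positive effects besides strength and balance, and adverse events". Falls during exercise with the application are followed up through the monthly fall questionnaire. For everything else the text says: "Additional adverse events of taking part in the intervention (eg, muscle strain) will be collected at assessments at 3, 6, 9 and 12 months". The instrument is a single item, "Have you experienced any negative effects of the exercise intervention", with predefined answers and an optional text field.

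Table 2 lists the same outcome as "Experienced negative effects of the exercise intervention§ (nominal scale, optional text field". Each of its time points carries an asterisk, which the footnote explains as "Only administered to the exercise intervention group". The § symbol in that row means descriptive analysis.

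Other health information comes from both arms. Under Data collection, "all participants will receive a request to report any falls during the past month by answering a short web-based questionnaire". Under Primary outcome, "If a fall is reported, additional questions will be asked about the cause of the fall, potential injuries sustained, need for medical attention and hospitalisation". Table 2 also gives both arms, at baseline and each quarter, the row "Health-related quality of life¶ (EQ-5D-5L", the chair stand self-test, self-rated balance and leg strength, and the fear-of-falling scale.

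**The concern.** Two features of the item combine.

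- **No comparator.** Strains, aches and new joint problems also occur in people aged 70 or over who do not use the application. Without a control-arm count, the exercise-arm percentage has nothing to be set against.
- **Built-in attribution.** The question asks about effects of the exercise, not about events. The Randomisation and blinding section says participants are not blinded. Someone with background pain may ascribe it to the programme, and someone strained by the programme may not make the link. The direction of the resulting error is unknown.

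This matters because of how the programme is meant to be used. Participants choose and progress their own exercises. The Background and Discussion argue for broad implementation without a health professional. A reader deciding on roll-out would want to know whether unsupervised use produces excess musculoskeletal problems. A later analysis plan could not supply that answer, because the control data would never have been collected.

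**Working it through.** The document gives no figure for this outcome, so there is nothing to reproduce. The check compares the stated data sources and then asks how precise a randomised comparison would be.

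**Step 1. Which harms have a count in each arm?**

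| Information | Exercise arm | Control arm | Counts events? |
|---|---|---|---|
| Falls (monthly) | yes | yes | yes |
| Injury, medical attention, hospitalisation after a reported fall | yes | yes | yes, fall-related only |
| Negative effects not arising from a fall | yes, self-attributed | no | exercise arm only |
| EQ-5D-5L, chair stand, self-rated balance and strength (quarterly) | yes | yes | no, status measures |

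The third row is the gap. With no control-arm count, neither a risk difference nor a risk ratio can be estimated for those events. The first two rows do not fill it, because the injury questions open only after a fall is reported. The fourth row does not fill it either, because a status score does not record who had an event, and benefit in some participants can offset harm in others.

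**Step 2. What would a parallel item deliver?** Take a common event proportion p in both arms and n responders per arm at one time point. The 95% CI half-width for the risk difference is

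1.96 × √(2 × p × (1 − p) / n).

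Inputs:
- n = 420 is the per-group number in the Sample size section. The planned minimum of 1400 gives 1400 / 2 = 700 per arm, so 420 is 60% of an arm.
- n = 350 is 50% of 700, matching the anticipated 50% attrition. n = 525 is 75% of 700.
- p is not given in the document. It is an assumption, shown from 10% to 40%.

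At n = 420:
- p = 0.10: 1.96 × √(0.18 / 420) = 1.96 × 0.0207 = 0.041
- p = 0.20: 1.96 × √(0.32 / 420) = 1.96 × 0.0276 = 0.054
- p = 0.40: 1.96 × √(0.48 / 420) = 1.96 × 0.0338 = 0.066

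At p = 0.20 with other response levels:
- n = 350: 1.96 × √(0.32 / 350) = 0.059
- n = 525: 1.96 × √(0.32 / 525) = 0.048

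In these scenarios the half-width lies between about 4 and 7 percentage points. It reflects sampling error only.

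**Step 3. A small inconsistency in the same row.** Table 2 as extracted also marks the negative-effects item at baseline, while the text lists only 3, 6, 9 and 12 months. Randomisation follows the baseline questionnaire, so an item restricted to the exercise arm could not be given then. Table and text should be reconciled.

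**The case against.** The strongest reply is that nothing the protocol claims depends on this item. It is labelled descriptive, the stated aims include no between-arm comparison of non-fall harms, and the primary analysis is untouched. It sits beside a parallel item on positive effects, also for the exercise arm only, so both can be read as describing users' experience of the application. This stands, and it limits the point to a missed opportunity.

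A reader might go further and infer that harms in general cannot be compared between arms, or that safety is not monitored. The documents do not support either reading. Falls, a central safety concern for unsupervised balance exercise, are the primary outcome in both arms. Injury, medical attention and hospitalisation after a fall are asked of both. Falls during exercise prompt contact from the research team. The quarterly status measures in both arms mean that a large net deterioration would not go wholly unseen, although they do not count adverse events.

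A further objection is that a parallel item would not give a clean comparison. Unblinded self-report with 50% anticipated attrition, and an acknowledged risk that attrition differs between groups, would add errors that the half-widths omit. That is correct and should be reported as a limitation. It does not make a one-arm, self-attributed percentage more informative than a randomised comparison with known weaknesses.

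Finally, controls cannot sensibly be asked about effects of an exercise programme they did not receive. That explains the present wording, and it is why the added item has to be neutral.

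**Conclusion.** The point holds for adverse events that do not arise from a fall. Text, table and footnote agree that these are collected from the exercise arm alone, through a question that requires attribution. The result will be an uncontrolled proportion whose bias could run either way. This is a stated design choice, not a detail left to a separate analysis plan.

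No stated inference is wrong, and the primary fall-rate analysis is unaffected. What is lost is an estimate that the existing questionnaires could provide with a half-width of about 4.1 to 6.6 points at 420 responders per arm. That range rests on assumed event proportions of 10% to 40%, equal in the two arms, and ignores reporting and attrition bias. The change is worth making because it is cheap and the data cannot be recovered after follow-up.

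**What to change.** - Add one neutrally worded item to both arms' existing 3-, 6-, 9- and 12-month questionnaires, asking about new muscle or joint problems or other health problems since the last questionnaire. Follow it with a question on whether the problem limited activity.
- Write answer options that suit both arms. The present predefined alternatives are not shown and belong to a question about the exercise, so they may not transfer.
- Keep the attribution question as a follow-up for the exercise arm.
- Report the proportion in each arm and the risk difference with a 95% CI. State that unblinded self-report and unequal attrition limit the comparison.
- Reconcile the baseline mark in Table 2 with the time points in the text.

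Cost: a slight extra burden for participants, some testing of the new wording with the reference group that tried the questionnaires, and one more results table. No staff or visits are added. If enrolment has begun, follow-ups already completed will lack the item, and the report should say which time points are covered.

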At the end of the 12-month intervention, the participants in both groups will be asked if they have started to do any other exercise activities or programmes during the intervention period. In addition, self-rated improvements in balance and leg strength over the whole course of the intervention will be measured through single-item questions. Both groups will also be asked to report if they have had any extra cost related to the intervention during the intervention period (eg, for internet access or equipment) to inform the cost-effectiveness analysis. Drop-outs and withdrawals from the study will be registered throughout the 12-month intervention. Withdrawals will be defined as those who have formally discontinued the study by filling in the withdraw questionnaire. Participants that consistently discontinue to answer the questionnaires will be defined as drop-outs.

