### Sample size

The sample size calculation for the primary outcome (fall rate over the 12-month intervention period) is based on the review of Sherrington *et al*^45^ by calculating for a fall rate of 1 fall/person year. In addition, a measure of over dispersion of 1.2 is used.^21^ Thus, we require 420 participants in each group to have an 80% power to detect a 20% reduction in fall rate at a 5% level of significance. We estimate that at least 1400 participants are needed based on a calculated attrition rate of 50% and a contribution of data from drop-outs. Due to uncertain drop-out rate, we will include up to 2000 participants.

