### Economic evaluation

Results will be presented as incremental cost-effectiveness ratio after 12 months, that is, the ratio of the difference in costs and the difference in health effects between the intervention group versus the control group. Data on health effects will be based on the primary outcome falls averted and the secondary outcome health-related quality of life assessed by the EQ-5D-5L. The data on health-related quality of life will be used to calculate quality-adjusted life years. Health and social care costs will be estimated by self-reported data on monthly falls and their consequences in combination with previously published data on the specific cost for the most frequent injuries. Resource use will include intervention costs, healthcare costs and community service costs.

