Adherence to individual exercise-based fall prevention is often poor over time.^10^ A contributing factor could be a lack of social components and peer support, which has been shown to positively affect attendance and adherence to exercise classes among older adults.^48^ However, preferences are diverse among older adults, and some older adults have stated to prefer home-based exercises.^15^ Due to the nature of this home-based intervention with online recruitment and an intervention period of 1 year, an attrition rate of 50% is anticipated. Still, this study will assess the effectiveness of a self-managed digital exercise programme to prevent falls in real-life settings where the older adults themselves will take the initiative to download and use an application. Hence, the attrition rates will be a valuable contribution in understanding more about older adult’s exercise adherence when exercising with smartphones and tablets in a home-based setting.

Home-based exercise has been shown to be preferred among older adults of advancing age, those with recent falls, and those with lower socioeconomic status.^15^ On one hand, fall prevention interventions delivered by digital technology might create a constraint for older adults who cannot afford digital technology or do not have digital competency. On the other hand, digital technology will present opportunities for older adults that might not have the opportunity or interest in attending community-based programmes or regularly visit healthcare centres. Additionally, in recent years, the use of digital technology such as smartphones and tablets has increased sharply among older adults. In 2019, 67% of the aged Swedish population used the internet on their smartphone, and 40% on their tablet,^49^ and the rapid increase in use is expected to continue. In light of these considerations, it is important to explore reach as suggested in the present study to describe which older adults that are interested in exercising with a digital application with no interaction with a healthcare professional.

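### Participants' own out-of-pocket costs are asked only at month 12, so under the expected 50% attrition about half of those randomised give no value for this one cost component

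*Protocol article*

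**What the plan says.** The protocol article fixes the timing of the participant-cost question in two places, and they agree.

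- Secondary outcomes introduces a group of items with "At the end of the 12-month intervention, the participants in both groups will be asked" and includes among them: "Both groups will also be asked to report if they have had any extra cost related to the intervention during the intervention period". The examples and purpose follow: "eg, for internet access or equipment) to inform the cost-effectiveness analysis".
- Table 2 lists the item as "Self-reported costs related to the interventions§ (amount and what", with a single mark in the 12-month column and a footnote sign for descriptive analysis.

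No earlier cost question is described, and none at withdrawal.

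On loss to follow-up, the Discussion says "an attrition rate of 50% is anticipated". The Sample size section builds on "a calculated attrition rate of 50% and a contribution of data from drop-outs". The definition in Secondary outcomes is "Participants that consistently discontinue to answer the questionnaires will be defined as drop-outs".

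The other economic inputs are collected during the year: falls and their consequences monthly, EQ-5D-5L at baseline and every three months. Secondary outcomes sets a societal perspective at 12 months. Planned statistical analyses uses all available data from each randomised participant and limits multiple imputation to variables with no more than 40% missing.

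**The concern.** A societal perspective brings participants' own spending into scope, and the plan says it collects the item for that analysis. Yet the item is asked once, at the point where the plan expects half the sample to have stopped answering. Someone who bought equipment or paid for internet access in the first weeks and then stopped never reports it. Someone who stays is asked to recall it up to a year later.

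At stake is the participant-cost part of the cost difference between arms. The exercise arm is the one asked to use a device several times a week, so spending, and its relation to dropping out, may not be alike in the two arms. The strengths-and-limitations list itself names a risk that attrition is unequal between groups. The gap cannot be closed after data collection, because the document describes no other source for drop-outs' own spending.

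**Working it through.** **Inputs.** Cost item at 12 months only (Secondary outcomes, Table 2). Attrition 50% (Sample size, Discussion). Randomised 1,400 to 2,000 (Participants, Sample size). Required 420 per group (Sample size). Imputation ceiling 40% (Planned statistical analyses). The document gives no completeness figure for the cost item and no curve of loss over the year, so the curve below is an assumption.

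**1. What the 50% means.** The requirement is 2 × 420 = 840 participants. At 50% attrition, 1,400 × 0.50 = 700 remain. The shortfall of 840 − 700 = 140 must come from the 700 drop-outs, or 140/700 = 0.2 each. The recruitment figure therefore treats attrition as loss of data, with partial data from drop-outs making up the difference. The month-12 cost item gets no such partial contribution.

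**2. Missing share against the ceiling.** Missing: 1,400 × 0.50 = 700, or 2,000 × 0.50 = 1,000. That is 50%, above 40%. Imputation would be allowed only with at least 1,400 × 0.60 = 840, or 2,000 × 0.60 = 1,200, answers at month 12.

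**3. Coverage, month 12 only against quarterly.** Let r3, r6, r9, r12 be the proportions still answering and T the observed person-time as a share of that scheduled. Month 12 only covers r12/T. Quarterly covers 0.25 × (r3 + r6 + r9 + r12)/T. The share with any cost report is r12 now and r3 with quarterly asking.

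| Assumed loss to 50% | r3, r6, r9, r12 | T | Any report: now, quarterly | Person-time covered: now, quarterly |
|---|---|---|---|---|
| Linear | 0.875, 0.750, 0.625, 0.500 | 0.750 | 50%, 87.5% | 0.500/0.750 = 67%, 0.6875/0.750 = 92% |
| Constant hazard | 0.841, 0.707, 0.595, 0.500 | 0.5/ln 2 = 0.721 | 50%, 84% | 0.500/0.721 = 69%, 0.661/0.721 = 92% |
| Early loss (illustrative) | 0.65, 0.60, 0.55, 0.50 | 0.6375 | 50%, 65% | 0.500/0.6375 = 78%, 0.575/0.6375 = 90% |

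The third row assumes 35% lost before month 3 and straight lines between visits: T = (0.825 + 0.625 + 0.575 + 0.525)/4 = 0.6375.

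**4. When the missing values bias the cost difference.** In an arm with missing share p, let R be the mean cost of responders and D that of drop-outs. Using responders alone gives an error of R − [(1 − p)R + pD] = p(R − D). The error in the between-arm difference is p_E(R_E − D_E) − p_C(R_C − D_C), with E for exercise and C for control. It vanishes if drop-outs and responders spend alike in both arms. It does not vanish in general if the gap R − D differs by arm, or if there is a gap and attrition is unequal. The document gives no cost figures, so neither its sign nor its size can be calculated.

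**The case against.** The strongest reply is that this is a small input to a secondary analysis. Table 1 admits only people who already have and regularly use a smartphone or tablet and who use email, so much spending on devices and internet probably predates enrolment. Table 2 marks the item as descriptive. The Economic evaluation section says "Resource use will include intervention costs, healthcare costs and community service costs" and does not name participants' expenses separately. One question covering the whole period spares burden in a trial that fears questionnaire fatigue. Month-12 EQ-5D-5L would pass the 40% ceiling at the same attrition, so missingness is a general problem, and its handling may sit in an analysis plan that is not shown. The coverage figures also describe data, not bias in the ratio.

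Much of this stands, and it limits the weight of the point. It does not remove it. The timing is fixed in this document rather than left open, and no analysis plan can recover answers that were never requested. EQ-5D-5L at least has earlier values from drop-outs to inform a missing-data model; this item has none.

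A reader might infer more: that drop-outs contribute no costs at all, so that the two sides of the ratio rest on different people. The documents do not support that. Economic evaluation derives health and social care costs from the monthly fall reports combined with published unit costs, and drop-outs supply those reports until they stop. Nor do the documents support a claim that the ratio would shift noticeably.

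**Conclusion.** The point holds for one component, participants' out-of-pocket costs. On the plan's own 50% attrition, about half of those randomised give no value. That exceeds the plan's imputation ceiling, and no other remedy is stated for this item. The missing-share result rests on the plan's attrition figure and on drop-outs giving no month-12 answer, as their definition implies; at 40% non-response or less, imputation would be open. The coverage gains rest on an assumed loss curve: quarterly asking raises the share with any report from 50% to between 65% and 87.5% across the three curves shown.

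The consequence for the cost-effectiveness ratio is unknown in size and direction and may be modest. This is a worthwhile, inexpensive improvement to a secondary analysis; it does not touch the primary outcome.

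**What to change.** Add the existing cost item (amount and what it was for) to the 3-, 6- and 9-month questionnaires in both arms, worded to cover the time since the last questionnaire. Keep it at 12 months and include it in the withdrawal questionnaire. Update Table 2 to match.

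Estimate 12-month participant costs with the same missing-data method as EQ-5D-5L: impute the unobserved quarters or adjust for censoring. Do not simply add up the observed quarters. That would count unobserved quarters as zero cost and understate the 12-month cost, unequally if attrition differs by arm. State also how the 40% ceiling applies. Under linear loss the quarterly items would be 12.5%, 25%, 37.5% and 50% missing, so the last quarter would still exceed it; under constant hazard the third would too, at 1 − 0.595 = 40.5%.

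The cost is one short item on three online questionnaires that already go to both arms, plus the withdrawal form. The downside is slight added response burden.
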